## Abstract

**Background:**

Patients with high-grade gliomas (HGG) often suffer from high distress and require psychosocial support. However, due to neurological and neurocognitive deficits, adequate assessment of distress and support needs remains challenging in clinical practice. The objective of the present study is to investigate whether a systematic implementation of signaling questions into the routine outpatient consultation will be helpful to bridge this gap.

**Methods/design:**

This is a multicenter cluster randomized study with two arms. Randomization is done on a cluster level with 13 hospitals providing regular neuro-oncological outpatient services conducted by neurologists and/or neurosurgeons. The intervention will include an assessment of psychosocial distress of patients in doctor–patient conversation compared to assessment of psychosocial distress via questionnaire (control, standard of care).

In total, 616 HGG patients will be enrolled. The outcome will be the number of HGG patients with increased psychosocial distress who receive professional support from psychosocial services.

Secondary endpoints are inter alia number of patients reporting psychosocial distress and unmet needs detected correctly by the respective method; quality of life; psychological well-being and burden of the patients before and after doctor–patient consultation; as well as the length of the doctor–patient consultation.

**Discussion:**

Patients with HGG are confronted with an oncological diagnosis and at the same time with high symptom burden. This often leads to distress, which is not always adequately recognized and treated. So far, only a limited number of adequate instruments are available to assess HGG patient’s distress. Yet, an adequate care and support network might facilitate the course of the disease and tumor therapies for patients. Our hypothesis is that an assessment conducted directly by attending doctors and in which the doctors talk to patients with HGG will be more effective than an assessment via a questionnaire, leading to better identifying patients in need of support. This may lead to an improvement of health care in these patients. Further, this method might be implemented also in other brain tumor patients (e.g., patients with brain metastases).

**Trial registration:**

German Clinical Trials Register, DRKS00018079. Registered on 3rd September 2019.

## Background

Neuro-oncological diseases, especially the diagnosis of a high-grade glioma (HGG), are associated with psychosocial burden. Patients face not only an oncological disease but also neurological symptoms resulting in changes of cognitive, role, and social functioning. Patients therefore often require support in terms of socio-legal counseling, rehabilitation, psychological support, and support regarding palliative care aspects [1]. Topics such as providing adequate psychosocial and supportive care in order to maintain quality of life are part of the available guidelines for the provision of neuro-oncological care [1]. As glioma patients suffer from cognitive impairment early during the disease trajectory [2, 3], adequate assessment of unmet needs and a regular psycho-oncological screening are recommended in the requirements for certification of Comprehensive Cancer Centers. However, an essential aspect is not only to record the supportive care needs but also to provide care.

In order to identify cancer patients in need of support, several psychosocial screening instruments such as the Distress Thermometer (DT) have been developed [4, 5]. The DT consists of a numerical analogue scale assessing distress and a problem list for assessing support needs. It has been validated for brain tumor patients and seems to be a reliable tool to identify burdened patients [4]. However, screening instruments have been rarely adapted to the diverse needs of neuro-oncological patients so far [6–8].

Especially as HGG patients suffer from neurocognitive deficits during their disease trajectory caused by the disease itself and the treatment, they may not always be able to complete the questionnaires [6, 9, 10]. Therefore, either adaption of instruments to the needs of neuro-oncological patients or alternative assessment approaches are required. As an alternative, we developed questions that can be asked during the doctor–patient consultation and that are understandable also for patients in reduced clinical condition, with neurocognitive deficits and/or physical restrictions.

Whether integrating these screening questions into the doctor–patient consultation (intervention arm) results in better identification of patients in need of psychosocial support compared to care as usual (CAU; comparison arm) is the primary research question of this trial.

### Objectives and hypothesis

This study was designed to assess whether the psychosocial assessment in patients with HGG can be improved by face-to-face assessment during doctor–patient consultation.

The following aims are addressed:
First, we compare the percentage of HGG patients in distress receiving adequate psychosocial careSecond, we compare the percentage of HGG patients correctly identified as distressed in the two trial arms

We hypothesize that more patients will be adequately assessed regarding distress during the doctor–patient consultation (intervention arm) than by the questionnaire assessment (CAU arm). We further hypothesize that HGG patients assessed in the intervention arm will more frequently receive support than the others. The PICO scheme for this trial is as follows:
Patients: Patients with high-grade gliomaIntervention: Assessment of distress in doctor–patient consultationComparison: Assessment of distress via questionnaireOutcome: Proportion of patients with high levels of distress who receive psychosocial care by specialized services

### Primary and secondary endpoints

The primary endpoint is the proportion of patients with increased psychosocial stress who receive professional support from psychosocial services (psycho-oncology, social services, cancer counseling centers, palliative care with psychosocial support).

Secondary endpoints are number of patients reporting psychosocial stress; number of patients receiving psychosocial care through specialized services such as psycho-oncology, social services, cancer counseling centers, palliative care, etc.; number of patients referred to care structures; quality of life; need for support; psychological well-being and burden of the patients before and after doctor–patient consultation; and duration of the doctor–patient consultation.

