**Fig. 1 Fig1:**
[figure not shown]
Course of the study

The clusters are the institutions (hospitals) participating in this trial (*n* = 13). In intervention arm hospitals, distress is assessed within the doctor–patient consultations. In CAU hospitals distress is assessed with the DT.

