#### Conditions of the intervention arm

Psychosocial distress is measured by three questions that emerged as important in a preliminary study. The three questions are:
Has your mood worsened due to the disease?Do physical changes due to the disease, such as numbness, weakness, or feeling exhausted more quickly, put a strain on you?Has your mental capacity worsened as a result of the disease, making it harder for you to concentrate or remember things, for example?

On the basis of the patient’s answers, the doctor offers psychosocial care, if indicated and desired by the patient, and refers the patient to the appropriate specialist services, e.g., psycho-oncological service, clinic social service, outpatient cancer counseling centers, physiotherapy, established psychotherapists, etc.

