#### Conditions of the control arm

In the control arm, psychosocial distress is assessed using the DT, which can be evaluated within a few minutes, so that the results in the control group can also be discussed during the doctor–patient consultation. If there is an obvious need for treatment or if a patient requires psychosocial support, the referral is carried out analogously to the intervention condition.

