### Instruments applied in the study

#### Before the doctor–patient consultation, t1

First patients complete a baseline questionnaire (t1) assessing use of and wish for psychosocial support using an adapted version of a self-developed questionnaire [17]. Further, the European Organization of Research and Treatment of Cancer Core Questionnaire (EORTC QLQ-C30) with its brain module (BN20) will be applied. It is a self-assessment tool to evaluate cancer patients’ quality of life. Validity and reliability have been previously tested in several clinical studies [18].

Patients in the control group complete additionally the DT. This is a self-reporting screening instrument, measuring psychosocial distress by a numerical rating scale accompanied by a 40-item list with problems from different areas of life, e.g., practical, family, emotional problems, etc. [5, 19].

Afterwards, the patients have the doctor–patient consultation. In the intervention group, the three questions, described above, are asked during doctor–patient consultation instead of using the DT (Table 1).

**Table 1 Tab1:** Operationalization of the outcomes and measurement points shown by outcomes

Outcome	Measure	t1	t2	t3
*Primary outcome: Psychosocial care through specialized services*				
Inpatient psycho-oncological service	Operation and procedure codes in the clinic information system or self-developed questionnaire			x
Cancer Counseling Center	Self-developed questionnaire			x
Inpatient social service	Operation and procedure codes in the clinic information system or self-developed questionnaire			x
Outpatient psychotherapy	Self-developed questionnaire			x
Neuropsychology	Medical records or operation and procedure codes in the clinic information system			x
Rehabilitation	Self-developed questionnaire or data derived from medical records			x
*Secondary outcomes*				
Percentage of patients that can be assessed for psychosocial distress	Participation rate in intervention arm vs control arm		x	
Length of doctor–patient consultation	In minutes (documentation by clinicians in the study worksheet)		x	
Emotional functioning/distress	EORTC QLQ-C30, emotional functioning scale	x		x
Health-related quality of life	EORTC QLQ-C30, global scale and BN20, all scales	x		x
Support requested	Self-developed questionnaire	x	x	x
Appointments arranged in specialized services	Documentation by clinicians in the study worksheet		x	

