#### After the doctor–patient consultation, t2

After the doctor–patient consultation, the patients complete the above mentioned questionnaire for support needs a second time.

In addition, the Structured Clinical Interview (SCID) for DSM (Diagnostic and Statistical Manual of Mental Disorders) is conducted with the patients. The SCID is used to identify mental health conditions [20]. The interviewer asks certain questions and codes the answers in order to be able to make a diagnosis at the end. The SCID is widespread, reliable, and valid [20]. The study nurses have been trained beforehand to conduct the interviews. Each controversial case will be discussed in a telephone conference with a supervisor (Table 1).

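### The primary endpoint counts only distressed patients, but its denominator is tied to no measure common to both arms, and the distress measures that the article names differ by arm

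*Protocol article*

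**What the plan says.** The section Primary and secondary endpoints reads: "The primary endpoint is the proportion of patients with increased psychosocial stress who receive professional support from psychosocial services". The section Statistical analysis keeps the same restriction to stressed patients and fits a hierarchical model with a random intercept for clinics, by intention to treat.

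Distress is measured differently in the two arms:

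- Conditions of the intervention arm: "Psychosocial distress is measured by three questions that emerged as important in a preliminary study".
- Conditions of the control arm: "In the control arm, psychosocial distress is assessed using the DT".
- Caption of Fig. 1: "In intervention arm hospitals, distress is assessed within the doctor–patient consultations. In CAU hospitals distress is assessed with the DT".
- Before the doctor–patient consultation, t1: "Patients in the control group complete additionally the DT", and "In the intervention group, the three questions, described above, are asked during doctor–patient consultation instead of using the DT". By design, then, no patient has both screens.

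Two related measures are taken in both arms. Table 1 lists "EORTC QLQ-C30, emotional functioning scale" at t1 and t3, in a row whose label also names distress. At t2, "In addition, the Structured Clinical Interview (SCID) for DSM (Diagnostic and Statistical Manual of Mental Disorders) is conducted with the patients". Table 1 places both under secondary outcomes, the SCID as the reference for screening accuracy. For the primary outcome, Table 1 operationalizes only the receipt of care.

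**The concern.** The intervention is a way of finding distressed patients. If being found distressed is also the condition for entering the primary analysis, the denominator is produced by the intervention after randomization. A screen that flags many patients brings in milder cases, who are less likely to receive care, and lowers its own arm's proportion. A screen that flags only clear cases raises it. The comparison would then mix the make-up of the flagged groups with the effect on care, and intention-to-treat analysis of the flagged patients would not restore the balance.

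The trial's own rationale expects the screens to behave differently. Its hypothesis is that more patients are adequately assessed in conversation, and its Background and Preliminary work sections say that impaired patients may be missed by questionnaires. The screens also differ in content: mood, physical change and mental capacity on one side, a numerical distress scale with a problem list on the other.

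**Working it through.** **1. The plan's own figure.** Inputs from Sample size: 15% versus 25%, α 0.05 (taken as two-sided), power 80%, ICC 0.005, 50 patients per clinic.

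- Per arm, unpooled variance: (1.960 + 0.842)² × (0.15×0.85 + 0.25×0.75) / 0.10² = 247.24.
- Design effect: 1 + 49 × 0.005 = 1.245.
- Total: 2 × 247.24 × 1.245 = 615.6, so 616 is reproduced.

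The planned effect is therefore 10 points, among stressed patients.

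**2. What a screen-defined denominator would do.** Let q be the share truly distressed, c1 and c0 the care rates in the truly distressed and in the others (the same in both arms, so no effect), and Se and Sp the sensitivity and specificity of a screen. The proportion receiving care among screen-positives is

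[Se·q·c1 + (1−Sp)(1−q)·c0] / [Se·q + (1−Sp)(1−q)].

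The document gives none of these inputs; all are assumptions. I took c0 = 5% and two pairs of screens:

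- Pair A: liberal (Se 0.90, Sp 0.50) against stricter (Se 0.70, Sp 0.80).
- Pair B: liberal (Se 0.95, Sp 0.30) against stricter (Se 0.70, Sp 0.85).

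Worked case, Pair B, q = 0.40, c1 = 30%:

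- Liberal: (0.38×0.30 + 0.42×0.05) / (0.38 + 0.42) = 0.135/0.80 = 16.9%.
- Stricter: (0.28×0.30 + 0.09×0.05) / (0.28 + 0.09) = 0.0885/0.37 = 23.9%.
- Difference: −7.0 points.

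Liberal minus stricter, in points (taken before rounding):

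| q | c1 | Pair A | Pair B |
|---|---|---|---|
| 0.40 | 25% | −3.1 | −5.6 |
| 0.40 | 30% | −3.9 | −7.0 |
| 0.50 | 25% | −2.7 | −5.0 |
| 0.50 | 30% | −3.4 | −6.2 |
| 0.60 | 25% | −2.2 | −4.1 |
| 0.60 | 30% | −2.8 | −5.1 |

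**3. When it vanishes.** With equal screens (Se 0.80, Sp 0.60 in both arms) the difference is 0; for example, 16.4% in each arm at q = 0.40, c1 = 25%. With care unrelated to distress (c1 = c0 = 20%), every screen gives 20% and the difference is again 0.

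**4. Sign.** If the three questions are the more liberal screen, the intervention arm looks worse than it is; if the DT is, it looks better. The document does not settle which applies.

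**The case against.** The strongest objection is that no passage makes screen-positive status the condition for entering the primary analysis. The arm-specific sentences describe how patients are screened, which is the comparison under test. The endpoint and analysis sections mention neither the DT nor the three questions. The section Objectives and hypothesis separates being in distress from being correctly recognised as such, which points to a reference outside the screen, and two candidates are measured in both arms. The full protocol (version 4.0 is cited) or an analysis plan may name one of them. All of this stands. A reader might infer that the denominator does rest on a different instrument in each arm, and that the proportions are therefore not comparable. The text does not support that as a statement of fact.

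A reader might also infer that patients unable to complete the DT leave the control denominator. No passage says so: the analysis is by intention to treat, and control-arm referral can follow from evident need.

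What does not stand is that this is only condensed detail. The article calls the arm-specific screens the measurement of psychosocial distress and gives the common measures only secondary roles. An analyst who followed that wording would build a biased denominator. The unrestricted count of patients receiving care, already a secondary endpoint, helps, but it does not repair the primary comparison.

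**Conclusion.** The concern holds as a conditional one. The primary denominator is linked to no common measure, while the named distress measures are arm-specific and are themselves the randomized contrast. If the arm's own screen is used, a spurious difference of roughly 2 to 7 points, in either direction, is possible against a planned 10. That range rests on assumed values: true distress 40–60%, care 25–30% in the distressed and 5% in the others, and the two pairs of screens above. It is not an estimate for this trial, and it is zero under the two conditions shown. Because the wording decides who counts in the primary endpoint, it should be settled before analysis.

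**What to change.** Define increased distress identically in both arms by a measure taken before the consultation and already collected in both, such as EORTC QLQ-C30 emotional functioning at t1 with a prespecified cut-off. State that neither the DT nor the three questions define the analysis set.

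Add:

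- A rule for patients who cannot complete the t1 questionnaire, for example SCID-based classification or imputation. This matters because the EORTC form is also self-completed, so the impaired patients who motivated the trial are those most likely to lack a score.
- SCID status as a sensitivity definition, noting that it is taken after the consultation in a non-blinded trial and covers mental health conditions only.
- Receipt of care among all enrolled patients as the supporting analysis, since it needs no distress denominator.

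The cost is wording and the missing-score rule; no new data are needed. The change also makes visible that the calculation counts all 616 enrolled patients although its rates apply to stressed ones. With a distressed share d (an assumption), 308·d patients per arm, 616·d/13 per clinic and ICC 0.005, power for 25% versus 15% is about 38% at d = 0.3, 55% at 0.5 and 68% at 0.7. Any distressed-only denominator has this consequence, so the fix does not create it.

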### Preliminary work

This is the first multicenter study with the aim to improve the health care situation of patients with HGG. We conducted several observational studies before that led to the research question of the GLIOPT trial. Hereby we found that:
Some questionnaires do not fit to the requirements of HGG patients [6, 11].Patients in reduced clinical condition with high unmet needs may be missed by a questionnaire or tablet assessment [8, 12].We can use “signaling items” probably indicating patients in need of support [13]. Applying these items in a face-to-face conversation between doctor and patient was possible. It seems, therefore, to be an alternative approach for distress assessment in this patient group.

Based on these studies, we developed the research question whether psychosocial care could be improved by face-to-face needs assessment during doctor–patient consultation compared to screening for distress using a questionnaire.

#### Development of “signaling items” for use in doctor–patient conversation

We developed questions regarding the burden and supportive care needs of glioma patients by a literature search, an expert survey, and patient interviews [14]:
Literature search: The research team analyzed the literature with regard to possible questions identifying supportive care needs in a doctor–patient consultation.Expert survey: Doctors who regularly see neuro-oncological patients were interviewed with regard to the importance of the questions identified from the literature.Pretesting: The preliminary questions were pilot-tested with ten patients. Afterwards, the questions were adapted accordingly.Patient interviews: Fifty patients were assessed using a structured interview. They estimated the importance of items and were asked to add missing items and to select the most important items of the preliminary questions. On the basis of the expert survey and patient interviews, three items/fields were identified by a weighted scoring procedure: psyche, body, and cognition.

#### Feasibility analyses of the three questions in clinical routine

The developed questions were applied in comparison to the questionnaires (EORTC QLQ-C30 + BN20, DT) in patients at different stages of the disease—perioperatively as well as in the outpatient setting [15]. Interviews were documented and the questions according to the results further adapted. The three questions are:
Has your mood worsened due to the disease?Do physical changes due to the disease, such as numbness, weakness or feeling exhausted more quickly, put a strain on you?Has your mental capacity worsened as a result of the disease, making it harder for you to concentrate or remember things, for example?

## Methods/design

### Study design

The study is a cluster-randomized, controlled, non-blinded, multicenter study with two parallel groups to be compared (Fig. 1). The study investigates the effects of two different ways of assessing psychosocial distress in outpatient HGG patients.

**Fig. 1 Fig1:**
[figure not shown]
Course of the study

The clusters are the institutions (hospitals) participating in this trial (*n* = 13). In intervention arm hospitals, distress is assessed within the doctor–patient consultations. In CAU hospitals distress is assessed with the DT.

#### Setting

Patients with HGG will be recruited from 13 geographically dispersed neuro-oncological centers throughout Germany (Tübingen, Mainz, Frankfurt, Ludwigsburg, Würzburg, München, Stuttgart, Köln, Düsseldorf, Berlin, Ulm, Trier, Leipzig). The time course is displayed in Fig. 2.

**Fig. 2 Fig2:**
[figure not shown]
GLIOPT SPIRIT figure. *SCID* Structured Clinical Interview for DSM (Diagnostic and Statistical Manual of Mental Disorders), *KPS* Karnofsky Performance Status, *NANO* Neurologic Assessment in Neuro-Oncology, *EORTC QLQ-C30 + BN20* European Organization of Research and Treatment of Cancer Core Questionnaire (EORTC QLQ-C30) with its brain module (BN20), *DT* Distress Thermometer

#### Randomization

The allocation to the two study arms is randomized. Through cluster randomization, the study is easier to implement into clinical routine compared to individual patient randomization. An external statistician who is not involved in treatment, planning, or evaluation of the study performed the randomization (Center for Clinical Studies in Mainz, Germany).

